### Qualitative phase

To explore a deeper understanding of mothers' views on the effect of implementing the study intrapartum care model, especially the components of the model that are more subjective such as respectful care or effective communication by the staff, in addition to data collection through questionnaires in the quantitative stage, interviews will also be conducted through open-ended questions with mothers of the intervention group 4–6 weeks after childbirth.

### Specific objective

Exploring the mothers' views on the effect of implementing the WHO intrapartum model on their childbirth process.

### Participants

Participants in this study will be women who had given birth (primiparous or multiparous) through the natural childbirth method with the WHO care model during childbirth and had passed 4–6 weeks postpartum, with a live and healthy infant. They will be also willing and able to describe their experiences of labor and childbirth. Purposeful sampling will be used for participant recruitment. Purposeful sampling allows the researcher to obtain rich information about a specific research question (44). Awareness of women's willingness to participate in the study will be achieved through telephone contact with the researcher. If they express interest in participating, a face-to-face meeting will be arranged at their preferred location, where the objectives and implementation process of the study, including their rights and the confidentiality of recording and storing the names and interview content, will be explained. Written informed consent will be obtained from the participants.

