### Blinding

It is noteworthy that the nature of this study does not allow for blinding the researcher and participants. To blind data collectors, the questionnaires for the postpartum stage will be completed by the researcher's assistant. Also, the data analyst will be blinded to group assignments.

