### Data collection

A semi-structured interview guide with open-ended questions will be used to explore and gain a better understanding of the topics and to elicit deeper insights from the participants Qualitative data will be collected through in-depth, semi-structured individual interviews with open-ended questions in an appropriate place the participants will choose. Conducting interviews with women will be done by the research assistant to avoid possible conflicts of interest. The questions to be asked are designed with the cooperation of the research team, and the ways to obtain valid data and focus on research questions are reviewed with the members of this team. The interview will begin with general questions such as, “How was your recent childbirth experience?” “Were you satisfied with the care you received during childbirth?” “To what extent did the childbirth care meet your expectations?” “What were the positive/negative factors in your childbirth experience?” Based on the type of response to each question, further probing will be done to find out the depth of the women's experiences, such as “Can you please provide more explanation and possibly give an example so that I can understand your point?”. Non-verbal data such as tone of voice, facial expressions, and body language of the participants will be also recorded by the researcher during the interview on a specific sheet, mentioning the time and location of the interview.

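### The qualitative sample is selected on birth outcome, the care-giver's role at the interview contradicts its safeguard, and the interview may precede the 6-week questionnaires in one arm

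*Protocol article*

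**What the plan says.** All references are to the Protocol article.

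- **Objective.** The qualitative phase is for "Exploring the mothers' views on the effect of implementing the WHO intrapartum model on their childbirth process" (Specific objective). It is not limited to any mode of birth.
- **Who is interviewed.** Interviews are held "with mothers of the intervention group 4–6 weeks after childbirth" (Qualitative phase). Participants are "women who had given birth (primiparous or multiparous) through the natural childbirth method with the WHO care model during childbirth" who "had passed 4–6 weeks postpartum, with a live and healthy infant" (Participants).
- **Who interviews.** "Conducting interviews with women will be done by the research assistant to avoid possible conflicts of interest" (Data collection, qualitative phase). The same section says that non-verbal data "will be also recorded by the researcher during the interview on a specific sheet".
- **Who the researcher is.** The Intervention section uses this term for the midwifery doctoral student who delivers the WHO model.
- **Blinding.** "To blind data collectors, the questionnaires for the postpartum stage will be completed by the researcher's assistant" (Blinding). The data analyst is also blinded; the participants and the researcher are not.
- **Questionnaires.** CEQ 2.0, PCQ, EPDS and PSS-I are completed after 6 weeks of follow-up (end of Routine care). All questionnaires are completed by interview (Data collection tools).
- **Use of the results.** The two strands are analysed separately and combined at interpretation (Study design).

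**The concern.** Three stated rules work against the purpose of the qualitative phase or of the outcome assessment.

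1. **Selection on outcome.** Eligibility depends on how the birth turned out. Normal vaginal delivery is a secondary outcome of the trial, and the newborn's condition is compared through the Apgar score. The women most likely to hold reservations about the model are those whose labour under it ended in caesarean or with an unwell infant. They are screened out, and the accounts that remain are then combined with the trial results.
2. **A safeguard contradicted in its own section.** The interview is given to the assistant to keep an interested party away, yet the person named as recording observations during it is the researcher. Read with the Intervention section, a woman asked whether she was satisfied with her care may be answering in front of the person who gave it.
3. **Order of contacts.** A conversation about the birth, held in one arm only, may come before interviewer-administered questionnaires on the same subject. CEQ 2.0 and PCQ measure two of the three primary outcomes.

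**Working it through.** **Selection.** Set the objective beside eligibility. The objective covers the model's effect on the childbirth process; eligibility covers natural births with a live, healthy infant. The Discussion itself expects that unpredictable high-risk conditions may disrupt the intervention, and women in whom this leads to a caesarean are the ones left out. The diversity criteria under Trustworthiness of the findings are age, education, occupation and socio-economic status. Mode of birth and infant outcome are not among them, so they do not repair the gap. The document gives no caesarean rate. If 10% to 30% of the 54 intervention women had one (an assumption), 54 × 0.10 = 5.4 to 54 × 0.30 = 16.2, or about 5 to 16 women, could not be interviewed.

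**Order of contacts.** The interview window is 4–6 weeks; the questionnaires follow 6 weeks of follow-up. The interview can therefore come first, and nothing in the text requires the reverse. Two consequences need different conditions:

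- *Priming* of a woman's answers needs only that her interview comes first, whoever conducts it.
- *Unblinding of the assessor* for that woman also needs the researcher's assistant (Blinding) and the research assistant (qualitative Data collection) to be the same person. The similar wording suggests this, but no section says so.

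**Which outcomes are exposed.** Only those collected by interview at the postpartum visit: CEQ 2.0, PCQ, EPDS, PSS-I, and the items on breastfeeding and on willingness to have another child. The delivery fear scale, labour durations, Apgar score and mode of delivery are recorded during or immediately after labour and cannot be affected.

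**How much it could matter.** The planning figure for childbirth experience reproduces. The difference is 3.25 − 2.71 = 0.54, SD 0.73, two-sided α 0.05 and power 95%. The normal approximation, n = 2(1.960 + 1.645)² × (0.73/0.54)² = 47.5, gives 48 per group. The t-test solution is 48.5, giving the plan's 49.

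Now suppose there is no true effect, k of 49 analysed intervention women are interviewed first, and their mean score shifts by b points. The arm difference becomes (k/49) × b. Neither k nor b is in the document. For k = 15 and b = 0.3:

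- arm difference: (15/49) × 0.3 = 0.092
- non-centrality: (0.092/0.73) × √(49/2) = 0.62
- two-sided rejection probability: 0.095

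| Women interviewed first (k) | b = 0.1 | b = 0.2 | b = 0.3 |
|---|---|---|---|
| 10 | 0.052 | 0.059 | 0.070 |
| 15 | 0.055 | 0.070 | 0.095 |
| 20 | 0.059 | 0.085 | 0.130 |

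Each entry is the type I error against a nominal 0.05. If a woman's questionnaires come first, her own outcomes are untouched.

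**The case against.** The strongest reply concerns blinding. A reader might infer that the blinded assessor conducts the qualitative interviews, so that every interviewed woman has an unblinded 6-week assessment and outcome blinding fails. The document does not support this. It never says that the two assistants are one person, and it never puts the interview before the questionnaires. Study design says that the two data sets are collected at the same time but independently. Staffing and visit order are also details that an article may leave to the full protocol. This part of the reply stands: unblinding can be raised only as a conditional risk. Nor is it the trial's only blinding, since the analyst is blinded too.

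Further points on the other side:

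- Participants know their arm and may disclose it in any case. Intervention women alone already see the researcher on days 10 and 40, so one-arm contact near the assessment is part of the intervention. This limits what the interview adds, but it does not justify a further avoidable contact on the very subject of the questionnaires.
- Taking only intervention women fits an objective about experiencing the model. This stands; it is not a defect.
- Excluded women still complete the quantitative questionnaires, and the strands are analysed separately, so the selection does not bias the randomised comparison. This stands. The selection affects the qualitative findings and the combined reading.
- The interview guide asks about negative as well as positive factors. It can draw these only from the women admitted.
- The qualitative sections may use the term researcher loosely for whoever does the work. That is possible, but the safeguard depends on who is present, so the wording needs to be settled.

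**Conclusion.** The concern holds in three limited parts.

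1. The eligibility rule selects on post-allocation outcomes that the stated objective does not call for. This is explicit in the text and tilts the qualitative account towards favourable births.
2. The qualitative Data collection section contradicts its own conflict-of-interest safeguard, if the researcher there is the person so named under Intervention.
3. The stated windows allow one-arm priming of CEQ 2.0, PCQ, EPDS and PSS-I in any woman interviewed before her questionnaires. Unblinding of her assessor is an additional risk only if the two assistants are the same person.

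The number of women affected cannot be derived from the document. The range of 0.052 to 0.130 for type I error rests wholly on assumed values of k and b, with an unchanged SD of 0.73 and 49 women per group. It shows that the risk runs from negligible to material; it does not estimate it. The cheapness of the remedy makes the change worthwhile.

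**What to change.** - **Participants:** open qualitative sampling to intervention women of any mode of birth and any infant outcome, and add both to the diversity criteria under Trustworthiness of the findings. If the restriction is kept, narrow the Specific objective to match it and state the limitation wherever the two strands are combined.
- **Qualitative phase and Participants:** invite a woman to the qualitative interview only after her 6-week questionnaires are complete. This removes both priming and assessor unblinding for her, whoever the assistants are.
- **Data collection (qualitative phase):** have the assistant, not the care-giving researcher, record the non-verbal notes.

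The cost is wording and scheduling, with no increase in the trial's sample size. The interview moves from 4–6 weeks to just after the 6-week questionnaires, so the stated window must be amended wherever it appears, including the Abstract. Interviews with women who had a caesarean or an unwell infant will need suitable care in the approach.

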### Data collection

A semi-structured interview guide with open-ended questions will be used to explore and gain a better understanding of the topics and to elicit deeper insights from the participants Qualitative data will be collected through in-depth, semi-structured individual interviews with open-ended questions in an appropriate place the participants will choose. Conducting interviews with women will be done by the research assistant to avoid possible conflicts of interest. The questions to be asked are designed with the cooperation of the research team, and the ways to obtain valid data and focus on research questions are reviewed with the members of this team. The interview will begin with general questions such as, “How was your recent childbirth experience?” “Were you satisfied with the care you received during childbirth?” “To what extent did the childbirth care meet your expectations?” “What were the positive/negative factors in your childbirth experience?” Based on the type of response to each question, further probing will be done to find out the depth of the women's experiences, such as “Can you please provide more explanation and possibly give an example so that I can understand your point?”. Non-verbal data such as tone of voice, facial expressions, and body language of the participants will be also recorded by the researcher during the interview on a specific sheet, mentioning the time and location of the interview.

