### Intervention

After assigning the participants to the study groups, socio-demographic and obstetrics characteristics questionnaires will be filled out for all of them. Then the researcher will implement the WHO intrapartum care model for those in the intervention group, whereas those in the control group will receive routine care by staff. The implementation of the study is in the form of multidisciplinary teamwork. The researcher who will implement the intrapartum care model is PhD student of midwifery (first author). She has attended workshops on making childbirth pleasant and physiologic childbirth and also worked for four years as a physiologic childbirth tutor in a health center. In the case where advice is needed or in unpredictable high-risk cases, the gynecologist involved in the study project will be contacted (second & fourth authors). The implementation of care will be monitored by the project supervisors who are reproductive health specialists (third and corresponding authors).

The intervention based on the 9 components of the WHO intrapartum care model is as follows:

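### The qualitative interviews are assigned to the research assistant to avoid a conflict of interest, but the text has the researcher, its term for the care provider, record non-verbal data during them

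*Protocol article*

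**What the plan says.** Four places in the protocol article bear on this.

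- **Qualitative phase, Data collection (interviewer).** "Conducting interviews with women will be done by the research assistant to avoid possible conflicts of interest".
- **Same section, last sentence (note-taker).** Tone of voice, facial expressions and "body language of the participants will be also recorded by the researcher during the interview on a specific sheet", together with the time and place of the interview.
- **Intervention.** "Then the researcher will implement the WHO intrapartum care model for those in the intervention group". The section goes on to identify this researcher as a midwifery PhD student.
- **Qualitative phase, opening paragraph.** "interviews will also be conducted through open-ended questions with mothers of the intervention group 4–6 weeks after childbirth". The aim is a deeper view of the more subjective parts of the model, with respectful care and staff communication as examples.

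The opening questions in the Data collection section include whether the woman was satisfied with her childbirth care and how far it met her expectations.

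**The concern.** The protocol recognises that the person who gave the care should not be the one asking women about it, and it sets a rule to prevent this. A later sentence in the same section appears to bring that person back as an observer. A woman may hold back criticism of how she was treated or spoken to when the person who looked after her in labour is taking notes on her expression.

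The components most exposed are the ones this phase is meant to explore. Muted criticism would produce themes more favourable to the model, and under Study design these are combined with the quantitative results at interpretation.

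**Working it through.** No arithmetic applies to the main point. The check is whether the statements can all be followed at once without the care provider attending the interview.

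1. **Does the recording task require presence?** Yes, for someone. The sentence places the recording "will be also recorded by the researcher during the interview on a specific sheet", and the items include facial expression and body language. These have to be watched as they occur; a later listening or a transcript would not supply them.

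2. **Who is the researcher?** The Intervention section gives the term to the person who delivers the model. The Blinding section says the researcher cannot be blinded and names a second person for outcome collection: "To blind data collectors, the questionnaires for the postpartum stage will be completed by the researcher's assistant". The Data collection section likewise uses separate labels for the assistant and the researcher. On the protocol's own usage, these are two people.

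3. **Whose care is being judged?** Only intervention-group mothers are interviewed, so each was in the group to which this researcher delivers the model. Under the companion component of the intervention, she may also act as a woman's companion when no one else is available and the woman agrees.

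4. **Is the care relationship over by then?** Often not. The continuity-of-care component schedules her last contact on day 40. Interviews fall at 4–6 weeks, that is 4 × 7 = 28 to 6 × 7 = 42 days. An interview held on days 28 to 39 comes before that last contact.

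5. **Does any other text remove the conflict?** No. The article nowhere says that the care provider stays out of the interview, or that the researcher in the closing sentence means the assistant.

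The literal reading therefore has the assistant asking the questions and the care provider observing. The rule on who conducts the interview is met in form, but its purpose is not.

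**The case against.** The strongest reply is that the closing sentence simply describes field notes, and that the researcher there means whoever holds the interview. The qualitative Participants section does use the word generically when it explains purposeful sampling. The Data collection section also states no rule on who is in the room; presence is inferred from the recording task. This stands as a real alternative. It means the care provider's attendance is a possible consequence of the wording, not an established fact. It does not remove the need to correct the text, since staff who follow the sentence as printed would defeat the safeguard.

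A second reply is that care is described as multidisciplinary and that the questions cover childbirth care as a whole, not one person's work. That is fair and softens the likely effect, but she remains the person who implements the model.

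A third reply points to the section on trustworthiness of the findings: member checking, team review of themes, and conditions that let women speak openly. These help with interpretation, but none can recover criticism that was never voiced.

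A reader might go further and infer that recruitment breaks the safeguard too, because "Awareness of women's willingness to participate in the study will be achieved through telephone contact with the researcher". The documents do not support that. The stated rule covers conducting the interviews only, so the call contradicts nothing. Moving it to the assistant would not end the relationship either, as the researcher already sees these women on days 10 and 40.

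**Conclusion.** The point holds as an inconsistency within one section. The interviews go to the assistant to avoid a conflict of interest, while the printed wording has the care provider record non-verbal behaviour during them.

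This rests on two assumptions: that the researcher has the same meaning here as in the Intervention section, and that recording during the interview means attending it. If both hold, the likely direction of bias is towards the intervention. Its size cannot be derived from the protocol.

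A reader might conclude that every interview is compromised and the safeguard lost. That would follow only if the literal reading is the intended one, which the text does not settle. Nor does the point reach the trial's quantitative results: the two phases are analysed separately, the postpartum questionnaires are completed by the assistant, and no sample size or test depends on this sentence. It is a correction that should be made, limited to the qualitative phase and the interpretation into which it feeds.

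**What to change.** In the qualitative Data collection section, reword the closing sentence so that the research assistant who conducts the interview also completes the non-verbal sheet, and add that the researcher who delivered the care is not present.

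This is a change of wording in one place. It needs no new staff, because the assistant already conducts the interviews. The downside is slightly more note-taking for the assistant while interviewing. No change to the recruitment call is needed on this ground.

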### Data analysis

The data obtained in this phase will be analyzed using qualitative content analysis. To this end, the researcher will read the transcript of the interviews several times to gain a general sense of the participant's experience. Then the objective words in the text that seem to convey the main thoughts or concepts will be identified for extracting the codes. After taking notes of the initial analysis and initial ideas and thoughts, the tags that reflect more than one main idea will be gradually extracted. The codes will then be classified based on their differences and similarities to form general categories.

Qualitative content analysis with a conventional approach will be used to analyze the data. Content analysis is a method for analyzing various types of data, such as visual and verbal data, and allows for the reduction of phenomena or events into defined categories to better analyze and interpret them. This method involves a deep understanding of the content through careful reading of sentences multiple times, identifying codes, searching for sub-themes, reviewing, and ultimately interpreting themes (45). The phrases and sentences related to the mothers' childbirth experiences will be coded on the margins of the coding sheets. Coding will be primarily based on the text using the mothers' descriptions. Then, codes with similar content will be gathered into sub-themes and themes. The authors will discuss and examine the interpretations of the mothers' descriptions of their childbirth experiences and reach an agreement on the themes.

